#### C. Self-care book

Participants in this group will be mailed a copy of *The Back Pain Helpbook*, a 224-page evidence-based book on self-care for back pain. The book includes information on causes of back pain, initiating a comprehensive fitness and strength program, and appropriate life-style modification and guidelines for managing flare-ups [24]. We believe that providing these materials may mitigate the disappointment among those randomized to "continued usual care". Such disappointment could conceivably bias reports of symptom severity and dysfunction and result in higher rates of loss to follow-up. Sending these participants a book also allows us to describe our study as a comparison of different lifestyle interventions, which helps create more uniform expectations for the different interventions.

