### Data collection and quality control

We will collect information on the outcomes at every stage of our recruitment, randomization, and treatment processes so that we can report patient flow according to the CONSORT guidelines [50]. Specifically, we will record the number of invitation letters sent, the number of responses received, the resolution of these responses (i.e., ineligible, refused, eligible and randomized, other), the number of participants assigned to each class who actually attended classes and the number of classes they attended, the number of participants in each treatment group providing each type of follow-up data at each follow-up (e.g., questionnaire, saliva samples), the number of withdrawals due to perceived ineffectiveness of the intervention, adverse experiences, loss to follow-up or other causes, and the number of participants completing the trial.

We will implement procedures to ensure that randomization is proceeding as planned, recruitment is on schedule, data collection forms are accurately entered into databases, the computer assisted telephone interviewing (CATI) system is storing data correctly and that data can be accurately transferred and retrieved as needed. We will develop a relational database to track information on every stage of recruitment, randomization, class attendance, and outcomes assessment so we can use standard automated reports of patient flow. All data system processes will be thoroughly tested prior to the start of recruitment.

The CATI programs will contain range and logic checks. Participant attendance information collected during the classes will be double key entered into a database that also contains logic checks. Prior to recruitment, all data systems will be tested with imaginary participants. Data will be examined for completeness using computer programs developed specifically for that purpose. In addition, we will test all analytic programs to ensure that the analyses are accurate.

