#### B. Statistical analysis

We will analyze outcomes from all follow-up time points in a single model, adjusting for possible correlation within individuals using generalized estimating equations (GEE) [55]. Because we cannot reasonably make an assumption of constant or linear group differences over time, we will include an interaction between treatment group and time point. In this case, the multivariate model that includes all time points provides very similar results to fitting separate analysis of covariance models over time and should not substantially influence statistical power.

We also plan to adjust for other baseline characteristics. Specifically, gender, age, pain traveling below the knee but not meeting the criteria for sciatica, job related activity, and Body Mass Index. In a randomized trial of this size, most baseline values and other covariates are unlikely to differ between randomized groups. However, inclusion of baseline covariates can improve the precision of the estimate and therefore increase power to detect differences.

We will use an intent-to-treat approach in all analyses, *i.e*., individuals will be analyzed by randomized group regardless of participation in any classes. This minimizes biases that often occur when participants not receiving assigned treatments are excluded from the analyses. The linear regression model (analysis of covariance) we will use is of the form:

where *Y*(*t*) is the response at follow-up time *t*, *Baseline *is the pre-randomization value of the outcome measure, *Trt *includes dummy variables for the yoga and exercise groups, *Time *is a series of dummy variables indicating the follow-up times, and *z *is a vector of covariates representing other variables being adjusted for. (Note that α_1_, α_2_, α_3_, and α_4 _are vectors.) The referent group in this model is the self care group at the first follow-up time. The models will be fitted using GEE to take into account possible correlation within individuals over time. For each follow-up time point that the omnibus *F*-test is statistically significant, we will go on to test whether there is a difference between yoga and self care to address Aim 1 and a difference between yoga and exercise to address Aim 2.

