Based on similar studies on this study population we expect to have at least a 90% follow-up rate which reduces the potential for bias due to loss of follow-up. Therefore, our primary analysis will be a complete case analysis including all observed follow-up outcomes, but we will adjust for all baseline covariates that are predictive of outcome, probability of being missing, or differences between treatment groups. We will also conduct sensitivity analyses using an imputation method for non-ignorable non-response to evaluate if our results are robust in the complete case analysis [56]. We will report both results in our manuscript.

To help us further understand the benefits of yoga as a treatment for back pain, we will explore possible interactions between treatment groups and covariates. For example, we will consider interactions of the treatment group and the baseline value that would indicate the effect of treatment depends on status at baseline. We will also test for significant interactions of treatment group with other variables (*e.g*., gender) to determine if treatment differences are modified by these variables. We will use similar methods to analyze secondary outcomes including disability days and satisfaction with care.

If we find that yoga is more effective than self care or exercise we will move to Aim 3 with the goal of exploring whether the beneficial effects of yoga on our primary outcomes are mediated through certain measured variables. As mentioned in Figure 1 and Table 4, we are interested in four major classes of measures that could mediate the effects of yoga on back pain outcomes: (1) physical function, (2) cognitive appraisal, (3) affect and stress, and (4) neuroendocrine function. In the interest of parsimony, we will narrow down the number of perspective variables within the four major classes of proposed mediators by using a modification of the framework described by Baron and Kenney [57].

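### The primary analysis does not secure the use of 6-week scores when a later visit is missing; if poor-response dropout differs between arms, the 12- and 26-week contrasts are modestly biased

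*Protocol article*

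**What the plan says.** All of this is in the protocol article, Statistical issues, part B (Statistical analysis), unless noted.

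- **Handling of missing outcomes.** "our primary analysis will be a complete case analysis including all observed follow-up outcomes, but we will adjust for all baseline covariates". Nothing is imputed in the primary analysis.
- **What accounts for missingness.** "we will adjust for all baseline covariates that are predictive of outcome, probability of being missing, or differences between treatment groups". All of these are baseline variables.
- **Model.** One GEE model covers weeks 6, 12 and 26, with a treatment-by-time interaction, the baseline value of the outcome and covariates. No earlier follow-up score is a predictor. The working correlation is not stated. The protocol says that "the multivariate model that includes all time points provides very similar results to fitting separate analysis of covariance models over time".
- **Sensitivity analysis.** "We will also conduct sensitivity analyses using an imputation method for non-ignorable non-response to evaluate if our results are robust". The next sentence adds: "We will report both results in our manuscript".
- **Expected loss.** At least 90% follow-up is expected. Part A (Sample size and the detectable difference) assumes 10% loss, not split by arm.
- **Data available.** Table 4 collects RDQ and bothersomeness at baseline and at 6, 12 and 26 weeks.

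**The concern.** If each visit is analysed on its own observed cases with baseline adjustment, the 12-week contrast is unbiased only when missingness at week 12 is unrelated to response after randomisation, given arm and baseline. A participant who does badly by week 6 and then leaves breaks that condition. The 6-week score that recorded the poor response counts in the 6-week comparison but need not inform the 12- or 26-week comparison. The arm that loses more such people then looks better later on.

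This mechanism is credible in an unblinded comparison of classes with a book. The reporting plan has a category for it, among "the number of withdrawals due to perceived ineffectiveness of the intervention, adverse experiences, loss to follow-up or other causes". The protocol also accepts that missingness can be predictable, since it adjusts for predictors of it, but it stops at baseline. The later Aim 1 and Aim 2 contrasts are at stake, because they rest on the primary analysis and not on the sensitivity analysis.

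**Working it through.** **1. Inputs from the protocol.** Baseline-adjusted RDQ SD 3.68; 210 participants at 2:2:1, so 84:84:42 randomised; 10% loss, so 75:75:38 evaluable; assumed yoga–exercise difference 1.7 points.

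**2. The plan's own figures.** The protocol gives no figure for bias from missing data, so I reproduced its RDQ power to confirm the inputs (two-sided 0.05 assumed, normal approximation).
- Yoga v exercise, 1.7 points: SE = 3.68 × √(2/75) = 0.601; 1.7/0.601 = 2.83; power = Φ(2.83 − 1.96) = 80.8%. Stated: 80%.
- Yoga v self care, 2.5 points: SE = 3.68 × √(1/75 + 1/38) = 0.733; 2.5/0.733 = 3.41; power 92.7%. Stated: 92%.
- Yoga v exercise, 2.5 points: power 98.6%. Stated: 98%.
- Omnibus F-test: 92.6%. Stated: 92%.

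The stated power holds and is not in question.

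**3. Assumptions not in the protocol.** The correlation ρ between the 6- and 12-week adjusted scores is 0.4 to 0.7. The log-odds of dropout after week 6 rise linearly with the standardised 6-week score x, with an odds ratio of 2 or 4 per SD. In the extreme case the worst 10% of scorers all leave.

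**4. Bias in one arm's observed 12-week mean.** Bias = ρ × 3.68 × E[x | stays], where E[x | stays] = ∫ x(1 − p(x))φ(x)dx / (1 − d), p(x) is the dropout probability and d the overall loss. At d = 0.10:

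| Dependence | E[x given stays] | Bias, ρ = 0.4 to 0.7 | Share of 1.7 |
|---|---|---|---|
| OR 2 per SD | −0.066 | −0.10 to −0.17 | 6% to 10% |
| OR 4 per SD | −0.116 | −0.17 to −0.30 | 10% to 18% |
| Worst 10% leave | −0.1755/0.9 = −0.195 | −0.29 to −0.50 | 17% to 30% |

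A negative bias makes the arm look better. A simulation of the first two rows gave 0.10 to 0.28 points (6% to 16%), the same within simulation error. The formula holds at week 26 with the 6- to 26-week correlation in place of ρ.

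**5. Bias in the contrast.** Simulated with 84 per arm, ρ = 0.6 and no true difference:

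| Loss, arm 1 v arm 2 | Mechanism | Observed cases only | Using week 6 |
|---|---|---|---|
| 10% v 10% | OR 2 in arm 1; random in arm 2 | about −0.15 | 0.00 |
| 10% v 10% | OR 4 in arm 1; random in arm 2 | about −0.25 | about 0.00 |
| 10% v 10% | OR 2 in both | about 0 | about 0 |
| 20% v 10% | OR 2 in both | −0.15 | −0.01 |
| 15% v 5% | OR 2 in arm 1; random in arm 2 | about −0.21 | 0.00 |

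The standard error was about 0.6 either way, so using the 6-week score cost no precision.

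**6. Type I error per pairwise test.** These figures ignore the omnibus gate; 4,000 replicates, Monte Carlo error about 0.0035; yoga–exercise and yoga–self care sizes.
- Mechanism in one arm only, 10% loss in each: 0.058 to 0.071.
- Same mechanism and rate in both arms: 0.050 to 0.054.
- 20% loss (OR 4) against 5% random loss: 0.095 to 0.124.
- Using the 6-week score, all scenarios: 0.043 to 0.058.

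**The case against.** **The GEE model may already use the 6-week score.** This is the strongest point, and it stands in part. A condensed article may leave the working correlation to the analysis plan, so its absence is not itself an error. A reader might infer that the 6-week score contributes nothing to the 12-week estimate, but the text does not say so. That is true under independence. With an exchangeable correlation estimated from the data (true ρ 0.6, odds ratio about 2.7 per SD in one arm, 10% loss), the 12-week bias fell from −0.21 to −0.02 or −0.03. What the article does fix points the other way: a complete-case label, baseline-only handling, and the statement that results resemble visit-wise models. Use of the score is possible but not secured.

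**The label.** Someone might also read complete case as excluding anyone with a missed visit. The same sentence includes every observed follow-up outcome, so that reading fails.

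**The protocol does not predict unequal loss.** This is correct. The remark "Such disappointment could conceivably bias reports of symptom severity and dysfunction and result in higher rates of loss to follow-up" concerns people left in usual care, and the book is supplied to lessen the disappointment. The list of withdrawal reasons is a CONSORT count, not a forecast. The 28% yoga drop-out in the Background comes from another trial, so bias computed at that rate is not this trial's scenario. Poor-response loss in the book arm would work against yoga, so no direction can be assumed.

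**Leaving classes is not leaving follow-up.** This also stands. Analysis is by randomised group regardless of attendance, and outcomes are collected by telephone. The 6-week score also cannot help for those who miss week 6 too.

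**The non-ignorable sensitivity analysis.** It is planned and will be reported, and since its imputation model is not described, nobody can say that it ignores the 6-week scores. It tests robustness but leaves the primary estimate as it is.

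**Conclusion.** The point holds as a modest weakness in the primary analysis. As written, the plan protects the 12- and 26-week contrasts only against missingness explained by arm and baseline, and does not commit to using follow-up scores it already holds.

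At the planned 10% loss, the bias in RDQ is about 0.1 to 0.3 points if dropout follows the 6-week score in one arm only, and about 0.5 points if exactly the worst scorers leave. It is near zero when mechanism and rate match across arms, and it grows with unequal loss. These figures rest on the assumed correlations and odds ratios and on all loss falling after week 6. Against a standard error of about 0.6, a bias of 0.15 to 0.25 is roughly a quarter to two-fifths of one standard error. That alone would not overturn a clear result, but it is avoidable.

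It does not follow that the planned analysis is biased in favour of yoga, or that the bias is certain to occur. The protocol supports neither statement.

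**What to change.** In Statistical issues, part B, keep the mean model (treatment by time, baseline value, covariates) and change how it is fitted. Either:

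- fit it by maximum likelihood as a repeated-measures model with unstructured within-person covariance; or
- keep GEE, applied after multiple imputation by arm that includes the 6-week RDQ and bothersomeness scores.

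At minimum, name a non-independence working correlation. This is the weaker option, because it removes the bias only so far as the chosen structure is close to the true one. Drop the complete-case label, which does not fit an analysis of all observed outcomes. Keep the non-ignorable imputation as the sensitivity analysis, since none of these changes deals with dropout driven by unobserved scores.

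The cost is a modelled covariance or an imputation step. Sample size, data collection and stated power do not change.

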We will first individually regress each of the potential mediators within a major class on the treatment group. If the potential mediator is associated with the treatment group (α-level = 0.10), we will then evaluate the magnitude of the effect of the individual potential mediator by using an inverse probability weighted (IPW) modeling approach on each of the primary outcomes (i.e., RDQ score or bothersomeness score)[58]. This approach allows us to estimate the direct effect of treatment after rebalancing the treatment groups with respect to the mediator. Specifically, we will first model the probability of the treatment given the mediator using logistic regression. From this model we will obtain the estimated probabilities that each person received their observed treatment given their observed mediator value. We will then use an inverse probability of treatment weighted regression to model the primary outcomes on treatment status while adjusting for the baseline level of the outcome. Comparing the weighted to the unweighted model will allow us to estimate how much of the direct effect of treatment on the outcome can be explained by a potential mediator.

We will do this for all potential mediators in a class and rank them based on how much of the direct effect of treatment on the outcome each explains. The potential mediators within a class that explain at least 10% of the direct effect will then be put in a multiple mediator weighted regression model to assess whether the effect can be mostly explained by a single mediator in the class or if it requires multiple mediators within the class. This stepwise approach will be used to reduce the number of mediators that will be included from a given class. It will not provide estimates of the final strength of the class of mediators since this would require the assumption that classes of potential mediators are independent of one another (i.e., physical function and stress are unrelated). Assessment of the strength of mediation from each class requires that we conduct a multiple mediator analyses evaluating all classes of mediators in a single model [59].

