After determining the subset of mediators to be included from each class, we will run a final multiple mediator IPW model. The application of the IPW approach, as compared to the traditional approach of adjusting for multiple mediators, allows us to more appropriately account for confounding between a mediator and the outcome both by additional mediators and by other measured variables [60]. Further we are better able to estimate the indirect effects of each mediator in a causal framework through decomposition of the total effect of treatment into indirect effects through each mediator and the direct effect after accounting for all mediators.

All time points for which there is a significant difference between yoga and self care (or exercise) will be included in the models, and we will use GEE to account for possible correlation within subjects over time.

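### The mediator screen and the weights leave out each mediator's baseline value, which costs screening power and can bias the share explained that is used for selection

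*Protocol article*

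**What the plan says.** The steps are in the protocol article, Statistical issues, B. Statistical analysis.

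- **Screen.** "We will first individually regress each of the potential mediators within a major class on the treatment group". A mediator goes forward if it is associated with treatment at an alpha of 0.10. No covariate is named.
- **Weights.** "we will first model the probability of the treatment given the mediator using logistic regression", which yields the "estimated probabilities that each person received their observed treatment given their observed mediator value". No covariate is named here either.
- **Outcome model.** The weighted regression is used "to model the primary outcomes on treatment status while adjusting for the baseline level of the outcome". That is the one baseline covariate named.
- **Selection.** The change in treatment effect between unweighted and weighted models ranks the mediators. "The potential mediators within a class that explain at least 10% of the direct effect" go into a model for their class, and the survivors go into a final multiple-mediator model.
- **Stated advantage.** For that final model, the weighting approach is said to "account for confounding between a mediator and the outcome both by additional mediators and by other measured variables". The other variables are not listed.

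Table 4 marks a baseline measurement for all the mediators: fear avoidance, self-efficacy, body awareness, distress, perceived stress, positive emotions, the Physical Impairment Index, cortisol and DHEA. The same section accepts that baseline covariates improve precision and power, but says so for the outcome models.

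**The concern.** Two things follow from leaving the baseline mediator out.

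First, the screen compares follow-up mediators with their full between-person variance. A real mediator that shifts moderately may be dropped, and no later step brings it back.

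Second, randomisation protects the treatment–outcome comparison but not the mediator–outcome relation. Suppose yoga moves the mediator. Weighting the arms until their follow-up mediator values match then makes their baseline mediator values differ. If that baseline value predicts later RDQ beyond baseline RDQ, the weighted treatment effect changes even when the mediator has no effect. The section presents weighting as a way to handle mediator–outcome confounding, yet the weight model that selects and ranks mediators contains no confounder.

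At stake is which mechanisms the trial puts forward for future research, above all in the yoga–exercise contrast, which the plan wants to use to isolate what is unique to yoga.

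**Working it through.** **Plan's own figures.** With n = 75:75:38 and RDQ SD 3.68 (A. Sample size and the detectable difference), two-sided alpha 0.05, noncentral t and F give:
- omnibus 92.6% (stated 92%)
- 2.5 points v self care 92.3% (92%)
- 2.5 points v exercise 98.5% (98%)
- 1.7 points v exercise 80.2% (80%)

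These reproduce. The mediator power of 0.86 and 0.83 cannot be checked, because its inputs are not given. The documents give no mediator SDs or correlations, so the values of d, r, g and ρ below are assumptions shown over a range.

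**1. Screen power.** Let d be the mediator shift in SD and r its baseline–follow-up correlation. Power = Φ(d / √[(1 − r²)(1/n₁ + 1/n₂)] − 1.645). The written screen corresponds to r = 0.

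For d = 0.4 and 75 v 38, √(1/75 + 1/38) = 0.199.
- Written: Φ(0.4/0.199 − 1.645) = Φ(0.36) = 64%.
- Adjusted, r = 0.6: Φ(0.4/(0.8 × 0.199) − 1.645) = Φ(0.87) = 81%.

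| | written | r = 0.3 | 0.5 | 0.6 | 0.7 |
|---|---|---|---|---|---|
| 75 v 38 | 64% | 68% | 75% | 81% | 88% |
| 75 v 75 | 79% | 82% | 88% | 92% | 96% |

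Noncentral t agrees to within about one point.

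**2. Share explained by an inert mediator.** Let g be the coefficient of the baseline mediator on follow-up RDQ given baseline RDQ (SD units), and ρ the correlation of the two baselines. Matching the arms on the follow-up mediator leaves their baseline mediators r·d apart. Adjusting for baseline RDQ removes a fraction ρ² of that. The false share is therefore about g·r·d·(1 − ρ²) / total effect.

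Take d = 0.5, r = 0.6, ρ of size 0.3, and total effects 2.5/3.68 = 0.68 and 1.7/3.68 = 0.46. For g = 0.2, 0.2 × 0.6 × 0.5 × 0.91 = 0.055, which is 8% of 0.68 and 12% of 0.46.

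| g | 0 | 0.1 | 0.2 | 0.3 |
|---|---|---|---|---|
| v self care | 0% | 4% | 8% | 12% |
| v exercise | 0% | 6% | 12% | 16–18% |

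The last cell is a range because the formula and large-sample simulation give 18% and a separate simulation 16%. At r = 0.7 the large-sample v exercise row is 0, 7, 14 and 21%.

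**3. Passing the 10% cut at trial size.** In simulation at r = 0.6, an inert mediator passes in 13% to 50% of trials v self care and 16% to 74% v exercise as g runs from 0 to 0.3. The lower ends are chance alone.

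**4. A real mediator.** With a true share of 33%, r = 0.7 and g of 0.2 to 0.3, the written weights return 46% to 53% in large samples. With the baseline mediator in both the weight and outcome models, the result is 33%.

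**5. Baseline mediator in the outcome models only.** For an inert mediator the bias goes, and about 10–13% pass the cut by chance. For a real mediator, matching on follow-up M leaves the baselines r·d apart. Holding the baseline fixed then restores a mediator difference of r × r·d = r²d. Only (1 − r²) of the real share is seen: at r = 0.6, 0.64 × 33% = 21%.

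**The case against.** **Level or change is not fixed.** The text speaks of an observed mediator value, and the hypotheses under Specific aims are worded as improvements and decreases. A reader might infer that the plan certainly uses the follow-up level; the text does not say so. Change scores would not cure the problem, however. In the same scenario with g = 0.29 the share becomes about −11% (v self care) and −16% (v exercise), so the bias reverses.

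**The false mediation is conditional.** A reader might infer that inert mediators will be selected as the mechanism. That needs treatment to move the mediator and its baseline to predict later RDQ beyond baseline RDQ, which the plan does adjust for. The documents give no value for that association. The screen's own 10% error rate, for a mediator that treatment does not move, is not inflated. This objection stands and limits the claim.

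**Aim 3 is exploratory.** The background and aims both say so, the stepwise procedure is described as a reduction device, and strength is left to the final model. This stands. But that model cannot recover mediators dropped earlier, and the selection steps are written out in enough detail to be judged.

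**Direct or total effect.** The 10% rule is phrased against the direct effect, and a reader might call that an error of definition. It is wording only: the weighted–unweighted comparison fixes the calculation, and the final decomposition is of the total effect.

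**More complex weights are noisier.** This is correct, and the fix takes account of it.

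**Conclusion.** The point holds in limited form. As written, the selection steps make no use of a baseline value that is collected for every mediator. The loss of screening power needs only a baseline–follow-up correlation in the mediator. For a 0.4 SD shift it is 3 to 4 points at r = 0.3, and 17 to 24 points at r = 0.7. The bias in the share explained needs a further association with outcome. Over the range examined at r = 0.6 it runs from zero to 12% v self care and to 16–18% v exercise, which is enough to straddle the 10% cut. All these sizes rest on assumed shifts and correlations.

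The documents do not support the inference that the efficacy conclusions are at risk: Aims 1 and 2 do not use these steps. The change is worth making because it improves a stated aim at almost no cost.

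**What to change.** 1. Say whether each mediator is analysed as a follow-up level or a change, and adjust the screening regression for its baseline value.
2. Include that baseline value as a covariate in both the unweighted and the weighted outcome models. This removes the false share of an inert mediator, with about 10–13% passing by chance. Used alone, it understates a real mediator by the factor 1 − r² shown above, so it guards selection but does not measure size.
3. Where the size or ranking of shares matters, put the baseline value in the weight model as well, with stabilised weights. The cost is more variable weights: about 18–27% of inert mediators then pass 10% by chance, against 13–16% under the written weights when there is no confounding. Report a bootstrap interval with each share rather than rely on the bare 10% cut.
4. Name the other measured variables in the final model.

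All the variables are already collected, so the cost is a few lines of analysis code, the bootstrap run and the extra weight variability in item 3.

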The power calculations are based on simple comparisons of the follow-up scores at a single point in time with adjustment for baseline values using analysis of covariance. We also plan to adjust for other baseline characteristics (e.g., age, gender, and baseline covariates found predictive of 10-week outcomes). Inclusion of such baseline covariates can improve precision of the variance estimate and therefore increase power.

Since assessment of Aim 3, the mediator analysis, is dependent on the results from Aim 1 and Aim 2, the study was not directly powered for Aim 3. We ran a simple power analyses for the primary mediator of interest, body awareness, assuming the expected sample sizes of 75:75:38, a single time point, and the RDQ Score as the outcome. We found a median power of 0.86 to detect body awareness as a significant mediator for yoga compared to self care and a median power of 0.83 for to detect body awareness as a significant mediator for yoga compared to exercise.

In summary, we have excellent power to detect a clinically meaningful difference on the omnibus test and the pairwise comparisons with self care for Aims 1 and 2 as well as adequate power to evaluate the yoga - exercise comparison for the mediator analysis for Aim 3. Although powered to detect a clinically significant difference on the RDQ, the resultant sample sizes will provide ample power for both of our primary outcome measures.

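### The final mediator model reports shares from the same data that selected the mediators, with no allowance for the selection, so those shares are biased upward

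*Protocol article*

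**What the plan says.** The procedure is in the protocol article under Statistical issues, section B (Statistical analysis). Aim 3 is entered once yoga is found better than self care or exercise. Each candidate is first regressed on treatment: "If the potential mediator is associated with the treatment group (α-level = 0.10), we will then evaluate the magnitude" of its effect by inverse probability weighting (IPW). Candidates are ranked by the share of the effect they explain. Those in a class that "explain at least 10% of the direct effect will then be put in a multiple mediator weighted regression model" go forward, and this step serves to shorten the list: "This stepwise approach will be used to reduce the number of mediators that will be included from a given class".

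The article limits what the stepwise step delivers: "It will not provide estimates of the final strength of the class of mediators". The reason it gives is that classes of mediators may depend on one another. Strength is therefore to come from the all-class model: "After determining the subset of mediators to be included from each class, we will run a final multiple mediator IPW model". The product of that model is a "decomposition of the total effect of treatment into indirect effects through each mediator and the direct effect after accounting for all mediators", described as causal.

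No hold-out sample, resampling, shrinkage or selection-adjusted interval is mentioned. Section A (Sample size and the detectable difference) names "the primary mediator of interest, body awareness". The text on mechanisms in the Background and the Specific aims both call this work exploratory.

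**The concern.** The second cut is applied to the estimated share, and the share is also what the final model reports. At 113 participants (75 + 38) or 150 (75 + 75) that estimate is noisy. Keeping only values of 10% or more keeps candidates whose chance error was favourable, and refitting on the same people carries the error forward as mediation.

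This is not detail left to an analysis plan, since the article writes out both thresholds and the order of steps. Aim 3 is meant to point later research at the most promising mechanisms. A mechanism that carries none of yoga's effect could be put forward with a sizeable share attached, and one that carries some could be overstated.

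**Working it through.** **Inputs from the protocol article.** Expected outcome data for 75:75:38; RDQ SD adjusted for baseline 3.68; effects of 2.5 points (yoga v self care) and 1.7 points (yoga v exercise); cuts of 0.10 and 10%. Tests are taken as two-sided.

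The Potential mediating variables section yields ten scores: fear avoidance, self-efficacy, two awareness questionnaires, distress, stress, positive states, the Physical Impairment Index, cortisol and DHEA. The seven physical tests, which may also be used singly, would make 17.

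**Assumed, because not given.** How far yoga shifts each score, and how each score correlates with outcome within arms.

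**Step 1: the article's own power figures.**
- Yoga v self care: SE = 3.68 × √(1/75 + 1/38) = 0.733; 2.5/0.733 = 3.41; power = Φ(3.41 − 1.96) = 92.7% (92.3% with the t distribution). Stated: 92%.
- Yoga v exercise: SE = 3.68 × √(2/75) = 0.601; 1.7/0.601 = 2.83; power = Φ(2.83 − 1.96) = 80.8% (80.2% with t). Stated: 80%.
- Omnibus test, noncentral F: 92.6%. Stated: 92%.

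The inputs are therefore read correctly. The mediator power figures of 0.86 and 0.83 cannot be reproduced, because their inputs are not stated.

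**Step 2: direction of the bias.** Let the estimated share be S + error, with the error averaging zero. For an inert score S = 0, yet its estimate at the screen, once kept, cannot be below 10%. The bias of a kept inert score at that step is therefore at least 10 percentage points by construction. In simulation the average was 12% to 28%.

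**Step 3: size.** The written steps were simulated at one time point in trials where yoga was significantly better, with ten scores whose true share is zero. Share = 1 − (weighted effect / unweighted effect). Ranges cover both comparisons. Two separately coded runs varied the shift:

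| Shift of each score | Trials in which any score passes (two runs) | Mean final share, given that one passes | Mean over all Aim 3 trials (first run) |
|---|---|---|---|
| 0 | 5-6%; 6-8% | 14% | 0.7-0.8% |
| 0.2 SD | 15%; 18-19% | 16-18% | 2.4-2.7% |
| 0.4 SD | 42-45%; 40-49% | 22% | 9-10% |
| 0.6 SD | 65%; 67-69% | 27-29% | 18-19% |

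The shares in the third column are from the first run; the second run gave 14-29% over the same shifts. The last column is the product of the first run's frequency and share, for example 0.42 × 22% = 9.2% and 0.45 × 22% = 9.9%.

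A third run, with independent scores, varied the correlation with outcome at no shift. At 0.3, some score passed in 32% (v self care) and 40% (v exercise) of trials, with mean shares of 21% and 23%. At 0.5 the figures were 31% and 41% of trials, with shares of 29% and 36%. With 17 candidates at 0.3, 52-55% of trials had a passing score. At a shift of 0.8 SD the mean share was about 50%.

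**Step 4: is selection the cause?**
- The same kept scores, estimated in independent data of equal size: −0.8% to 1.4%.
- No selection: −0.5% to 2%.
- Four scores fixed in advance: −1% to 0%.

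The excess comes from selecting and estimating on the same data, not from the weighting.

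**Step 5: several time points.** The article includes every time point with a significant difference. With three (assumed within-person correlations 0.5 for outcome and 0.6 for mediators), some score passed in 31% of trials at 0.4 SD, against 48-51% with one time point in the same code. At no shift it was 1-2% against 5-8%. The mean share given selection stayed at 19-20%.

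**Step 6: a real mediator.** With one score truly carrying 30% and nine inert, the final model averaged 38-39%, an excess of 8 to 9 percentage points.

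**Not simulated.** The within-class reduction, for which the article gives no dropping rule, and adjustment for other measured confounders.

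**The case against.** The strongest reply is that the article already limits the claim. Mediator work is called exploratory, Aim 3 was not directly powered, and the stepwise step is said not to give final strength. A lenient screen suits hypothesis generation, and nothing in Aims 1 or 2 depends on it. This stands as a limit on the consequence. It does not remove the bias: the disclaimer concerns dependence between classes, and the model it defers to uses the same selected scores and the same data.

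A reader might infer that mediators explaining nothing will be reported as explaining about a fifth of the effect. The documents do not support that. The figure applies only after an inert score passes both cuts. It depends on shifts and correlations that the article does not give, and at no shift more than nine trials in ten select nothing. A reader might also infer that the planned intervals are too narrow, but the article specifies no interval.

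It is also fair that fixing scores in advance removes the bias but not the noise. At 0.4 SD and one time point, four fixed inert scores still showed a share of 10% or more in 22-25% of trials (SD 15-17 points). The answer is to show intervals rather than keep the selection.

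**Conclusion.** The point holds in limited form. The written rule selects on the estimated share and then reports that share from the same participants, so final-model shares are biased upward. The direction follows from the rule itself; the size does not come from the documents. For ten inert scores, one time point and shifts of 0 to 0.6 SD, a set that passes both cuts is credited on average with roughly 15-30% of yoga's effect. That occurs in about 6-8% of trials at no shift and 40-49% at 0.4 SD, and less often when several time points qualify. Stronger correlation with outcome or larger shifts push the conditional share above that range. The consequence is confined to the exploratory Aim 3, but it bears on what that aim is for: ranking mechanisms for later study.

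**What to change.** 1. Keep the two-cut screen as a descriptive, hypothesis-generating step.
2. Report the estimated share and its interval for every candidate, selected or not.
3. Take the reported shares from a model whose mediators do not depend on the screen, for example all prespecified scores, with body awareness always included.
4. If the screened model is also shown, label its shares as conditional on selection. Give intervals and an optimism correction from a bootstrap that repeats the whole screen in each resample.

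The cost is analysis-plan wording, more computing, wider intervals and smaller reported shares. Weights built on ten scores may be unstable against self care, where 38 participants leave about 3.8 per score (38/10), so the weights should be inspected.

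Sample splitting and one score per class are optional. Halving the sample cuts the 0.10 screen's power for a 0.4 SD shift from 64% to 40% (75:38 to 37:19) and from 79% to 52% (75:75 to 37:37). One score per class narrows hypotheses 3, 4 and 6, which each ask about several variables.
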